### Randomization and allocation concealment

2.6

To avoid selection bias, an independent statistician, who will not be involved in any other part of the study, will randomly allocate eligible participants to the acupuncture group or the control group in a 1:1 ratio using the SPSS 25.0 software. Grouping will be performed based on stratified randomization, in which baseline variables such as gender, age, and presence of ST-segment elevation myocardial infarction will be used as baseline characteristics to balance the two groups. Opaque envelopes will be used to store the randomization scheme and will be opened successively according to the enrolment order. Grouping of patients will be determined according to the allocation scheme in the envelope. After opening the envelope, the assigned intervention will only be disclosed to the treating acupuncturist, whereas other researchers and the medical staff will remain blinded. Participants will receive treatment in separate rooms throughout the trial period to prevent communication.

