#### Primary outcome

2.9.1

The primary outcome is the incidence of SF-NR and will be calculated as follows: Incidence of SF-NR = (number of cases with no-reflow + number of cases with slow flow)/total number of cases × 100%. SF-NR will be determined based on the CTFC and TIMI flow grade criteria. Two experienced cardiologists will independently assess slow flow (TIMI grade 2 or CTFC > 27 frames) and no-reflow (TIMI grade 0–1 or CTFC > 40 frames) immediately after PCI stent implantation for patients without dissection, thrombus, or spasm (44). The recordings will be conducted at a rate of 30 frames per second, and the CTFC of the left anterior descending artery will be calculated by dividing the number of frames by 1.7 (45). In the case of disagreements, data will be reassessed jointly to reach a consensus.

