### Calculation of sample size

2.12

Since previous RCTs have not investigated acupuncture as an adjunct intervention for managing SF-NR in the AMI patients during PCI, it is challenging to determine the optimal sample size through power calculation. Therefore, instead of a formal sample size estimation, this trial will use a preliminary exploratory clinical pilot design for estimating the sample size (47). However, to preliminarily assess the feasibility of acupuncture-assisted PCI to prevent SF-NR, we will meticulously ensure adequate number of participants in our experimental design by adhering to the established guideline of a minimum of 12 participants per group for pilot studies (48). A previous study suggested that each group should have a sample size ranging from 20 to 25 cases for exploratory clinical trials assessing the effectiveness of intervention measures (49). Therefore, in this study, each group consisted of 25 patients and a total of 50 cases for the 2 groups. However, to account for a dropout rate of 20%, this study will recruit 60 patients (30 patients per group). It seems plausible that the dropout rate would be less than 20% because of the short duration of the procedure and the high requirement of surgery among the participants (50). The results of this study will contribute to providing the effect size data for calculating sample sizes in the further large-scale RCTs.

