### Statistical analysis

2.15

Statistical analysis will be performed according to the intention-to-treat (ITT) principle using the SPSS V.25.0 software (IBM Corporation, Armonk, New York, USA). Missing data will be addressed through multiple imputations. *P* < 0.05 will be considered as a statistically significant difference between groups. The normally distributed data will be presented as Mean ± SEM. The inter-group comparisons for this data will be performed using the independent sample t-tests and paired t-tests will be used within-group comparisons. Non-normally distributed data will be presented as median (interquartile range) and the independent sample non-parametric tests will be performed for comparing the data between group. Count data will be expressed as frequency (percentage) and analyzed using the chi-square test. Ridit analysis or rank sum tests will be used to assess the ordinal data.

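### Randomisation is stratified by gender, age and STEMI, but the only test named for the primary outcome ignores those factors; the result is a conservative test with a modest loss of power

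*Protocol article*

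**What the plan says.** Randomization and allocation concealment (2.6) describes 1:1 allocation and says: "Grouping will be performed based on stratified randomization, in which baseline variables such as gender, age, and presence of ST-segment elevation myocardial infarction" serve as the balancing characteristics. The list is open-ended and age has no cut-point. On the mechanics, the same section says: "Opaque envelopes will be used to store the randomization scheme and will be opened successively according to the enrolment order". It does not say how many sets of envelopes there are.

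The outcome section (2.9.1) states: "The primary outcome is the incidence of SF-NR". This is a proportion of patients, so it falls under the rule for count data in Statistical analysis (2.15): "Count data will be expressed as frequency (percentage) and analyzed using the chi-square test". No stratified test and no adjusted model is named there for any outcome. The threshold is P below "0.05 will be considered as a statistically significant difference between groups".

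Calculation of sample size (2.12) gives no power calculation. It follows rules of thumb for pilot trials, under which "each group consisted of 25 patients and a total of 50 cases for the 2 groups", raised to 60 for dropout. It says the results will supply effect-size data for later, larger trials.

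**The concern.** Stratified allocation forces the arms to be alike on the stratifying factors. If those factors predict SF-NR, the difference between arms then varies less from trial to trial than under simple randomisation. A plain chi-square test does not use this: it takes its variance from the pooled proportion, as if the factors had been left to chance. The variance is then too large, the P value too high on average, and the precision that stratification was meant to buy is lost.

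At stake are some power in a trial that declares significance at 0.05 and, more usefully for a pilot, the interval around the effect estimate that is to inform later trials. Validity in the sense of false-positive control is not at stake.

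An unseen statistical analysis plan could add adjustment. But the article is not silent here: it names a test, and that test does not match the design.

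**Working it through.** **Inputs from the article.** 60 patients, 30 per group (2.12); 1:1 allocation and the three factors (2.6); binary primary outcome (2.9.1); alpha 0.05 (2.15), taken as two-sided; SF-NR in 41% of cases (Introduction).

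**Assumptions, not in the article.** The share of STEMI patients and the SF-NR rate by stratum. They are varied below, with the overall rate kept at about 41%.

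**Step 1: the plan's own figure.** 25 × 1.2 = 30 per group, 60 in total, reproduces the recruitment target. There is no stated power or effect size to reproduce.

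**Step 2: size of the chi-square test by formula.** Take 40 STEMI and 20 non-STEMI patients, balanced as 20+20 and 10+10, and no treatment effect. Let p1 and p2 be the SF-NR rates in the two strata, and p = (2·p1 + p2)/3.

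- True variance of the difference: (2/30)·W, with W = [2·p1(1−p1) + p2(1−p2)]/3.
- Variance the chi-square uses: about (2/30)·T, with T = p(1−p).
- Actual type I error: about 2·[1 − Φ(1.96/√(W/T))].

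| p1 / p2 | Odds ratio | W | T | W/T | 1.96/√(W/T) | Type I error |
|---|---|---|---|---|---|---|
| 45% / 33% | 1.7 | 0.2387 | 0.2419 | 0.987 | 1.973 | 4.8% |
| 50% / 23% | 3.3 | 0.2257 | 0.2419 | 0.933 | 2.029 | 4.2% |
| 55% / 13% | 8.2 | 0.2027 | 0.2419 | 0.838 | 2.141 | 3.2% |
| 60% / 5% | 28.5 | 0.1758 | 0.2431 | 0.723 | 2.304 | 2.1% |

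**Step 3: simulation of the same setting** (200,000 trials per row). Power is for a halving of SF-NR in each stratum. CMH is the Cochran-Mantel-Haenszel test stratified by STEMI, without continuity correction.

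| p1 / p2 | Type I: chi-square / CMH | Power: chi-square / CMH | Power lost (points) |
|---|---|---|---|
| 45% / 33% | 4.7% / 4.8% | 40.1% / 40.7% | 0.6 |
| 50% / 23% | 4.1% / 4.6% | 40.2% / 42.3% | 2.1 |
| 55% / 13% | 3.1% / 4.8% | 39.5% / 44.5% | 5.0 |
| 60% / 5% | 2.0% / 4.8% | 40.0% / 48.3% | 8.3 |

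The simulated type I errors agree with the formula.

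**Step 4: all three factors.** Eight strata (age split in two), permuted blocks of 4 within strata, 75% male, 50% older, 60% STEMI, and each factor with the same odds ratio for SF-NR; 6,000 trials per cell, treatment odds ratio 1 or 0.25. CMH here uses all eight strata.

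| Factor odds ratio | Type I: chi-square / CMH | Power: chi-square / CMH | Power lost (points) |
|---|---|---|---|
| 1 | 5.0% / 4.7% | 62.8% / 61.4% | −1.4 |
| 2 | 4.9% / 5.4% | 59.4% / 60.6% | 1.2 |
| 3 | 3.7% / 4.8% | 54.8% / 58.4% | 3.6 |
| 5 | 2.9% / 4.5% | 45.8% / 54.9% | 9.0 |

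Under no treatment effect, the mean estimated risk difference was within 0.2 percentage points of zero in every stratified scenario. With non-prognostic factors, CMH over eight strata is slightly worse than the chi-square.

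**Step 5: stratum size.** 2 × 2 × 2 = 8 strata; 60/8 = 7.5 patients each, or 50/8 = 6.25 evaluable. A test over the full cross would be sparse.

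**Step 6: if allocation were not stratified.** With one unstratified list and the last three settings of step 3, the chi-square type I error is 5.0%, 4.9% and 4.9%, and the power gap to CMH is 1.5, 3.9 and 6.7 points.

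**The case against.** The strongest reply is that little is lost. The error is on the safe side, the trial is a pilot sized without a power calculation, and no stated target depends on a few points of power. The article gives no SF-NR rate by STEMI status, and the settings with a marked loss need odds ratios of about 8 to 28 for one factor, or 5 for each of three. With weak predictors the two tests are practically the same. All of this stands, and it limits the size of the point. It does not remove the mismatch between how patients are allocated and how the outcome is tested.

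It can also be said that stratifying the test by STEMI alone leaves out two of the named factors. That is true: the test would stay somewhat conservative if sex and age are prognostic. It is a compromise forced by strata of about seven patients, and the choice of STEMI is a clinical judgement, not a result in the article. The supporting model covers the other two factors.

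A reader might go further and infer, from envelopes that "will be opened successively according to the enrolment order", that there is a single sequence, so that the promised stratification cannot have been delivered and adjustment is needed all the more. The article does not support this. It never says there is one sequence; separate sets for each stratum, each opened in order, fit the sentence, and a condensed article may leave such logistics to the full protocol. Nor would the consequence follow for validity: under one unstratified list the chi-square has its correct size (step 6), and the possible gain in power from adjustment is slightly smaller, not larger. The conservative type I error arises only if stratification worked, so it cannot be combined with a claim that it failed.

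**Conclusion.** The point holds in a limited form. The article stratifies the randomisation and then names, for the primary outcome, a test that ignores the strata. If stratification works and the factors are prognostic, the test is conservative: type I error of about 2% to 4% in place of 5%, and a power loss of about 0 to 4 points for weak to moderate predictors and 5 to 9 for strong ones. If the factors are not prognostic, nothing is lost. There is no inflation of false positives and no bias under the null.

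These sizes rest on an assumed STEMI share, stratum rates and, in step 4, age split and block size; only the 41% overall rate and the 60 patients come from the article. The direction follows from the design; the size cannot be fixed from the article. Nothing here shows that the allocation was carried out wrongly.

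**What to change.** Name as the primary analysis the Mantel-Haenszel risk difference with a 95% confidence interval, and the Cochran-Mantel-Haenszel test, both stratified by STEMI only. State whether a continuity correction is used; the figures above use none. Support this with a logistic model containing STEMI, sex and age (age as a continuous variable), using a penalised (Firth) fit if events are few. Adjust the continuous outcomes for the same three factors.

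In 2.6, as a clarification only, close the list of factors, give the age cut-point, and say how the envelopes are organised by stratum.

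The cost is wording. The factors must be known at randomisation, so no patients and no new data are needed. The Cochran-Mantel-Haenszel test is available in the planned software; a Firth fit needs an add-on. The article reports recruitment as ongoing, so the change should be made before unblinding. The downside is small: slight or no gain if the factors turn out not to be prognostic.

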### Blinding

2.7

At recruitment, participants will be informed that they will have an equal chance of receiving EA during PCI. The acupuncturists and participants cannot be blinded because of the nature of the acupuncture intervention but steps will be taken to minimize bias resulting from single blinding as much as possible. Acupuncturists will receive specialized training before participating and will be prohibited from discussing the treatment procedures and outcomes and will not participate in the evaluation of results. Patients will be treated separately to prevent contact between participants. The randomization staff and acupuncturists will have access to the assignment information but the outcome evaluators and statisticians will remain blinded throughout the entire clinical trial. Statisticians will speculate on the grouping allocation before data analysis to assess the blinding efficacy and unblinding will only occur after completion of the data analysis.

Emergency unblinding will only occur in the event of severe AEs that would require immediate identification of the patient treatment, including details about severe infection, uncontrollable pain, unexplained death, or similar situations.

### Interventions

2.8

#### Control group (standard PCI treatment)

2.8.1

(1)*Fundamental nursing care*: This will include educating the patients regarding bed rest, avoiding overexertion, regulating diet, strictly avoiding smoking or alcohol consumption, monitoring vital signs, nutritional support, administering oxygen as appropriate, and timely management of the AMI-related complications.(2)*PCI operation:* All patients will undergo PCI under local anesthesia after signing informed consent. Following standard coronary angiography, PCI will be performed by at least two experienced interventional cardiologists according to the 2021 ACC/AHA/SCAI Guideline for Coronary Artery Revascularization (37). The right radial artery approach will be preferred, but the femoral artery approach will be used in cases of contraindications. Intravenous heparin will be administered to maintain an activated clotting time (ACT) of above 250 s during the procedure. Stent selection and quantity will depend upon the vascular conditions and judgment of cardiologists. Thrombolysis in myocardial infarction (TIMI) flow grades and corrected thrombolysis in myocardial infarction frame count (CTFC) will be calculated post-stent implantation to assess the coronary artery blood flow and the incidence of SF-NR.(3)*Routine drug treatment:* This will be according to the 2017 European Society of Cardiology (ESC) Guidelines for the Management of Acute Myocardial Infarction in Patients Presenting with ST-segment Elevation and the 2016 Guidelines for the Diagnosis and Treatment of non-ST-segment Elevation Acute Coronary Syndrome by the China Society of Cardiology of Chinese Medical Association (38, 39). Unless contraindicated, all patients will be administered 300 mg aspirin, 180 mg ticagrelor, and 40 mg atorvastatin before PCI. Postoperatively, patients will be prescribed secondary prevention medications, including aspirin (100 mg daily), clopidogrel (75 mg daily) or ticagrelor (90 mg twice daily), atorvastatin calcium tablets (20 mg nightly), angiotensin-converting enzyme inhibitors (ACEIs), angiotensin II receptor antagonists (ARBs), Beta-receptor blockers, and low-molecular heparin. The dose adjustment will be according to patient's condition.

#### Acupuncture group (intraoperative acupuncture-assisted PCI treatment)

2.8.2

Patients in the acupuncture group will receive the same treatment as the control group. They will also receive intraoperative EA that will be administered to the AMI patients without interfering with the PCI procedure.
(1)*Acupoints*: As shown in Figure 2, left Neiguan (PC6) and Ximen (PC4) were chosen as acupoint locations based on the Nomenclature and Location of Acupuncture Points (GB/T 12346-2006), a standard of the People's Republic of China(2)*Implementation:* In the cardiac catheterization laboratory for PCI, the acupuncturist will sterilize the skin in the local area of the left Neiguan (PC6) and Ximen (PC4). Then, sterile disposable stainless steel acupuncture needles (1.5-inch Hua Tuo brand, *ϕ* 0.30 × 40 mm; Suzhou Medical Appliance Factory Ltd.) will be inserted vertically to a depth of 0.5–0.8 inch. Acupuncture manipulation, such as lifting and twisting, will be used until the De Qi sensation is felt. The EA therapeutic instrument (low-frequency electronic pulse therapy instrument, model G6805-2A, Shanghai Huayi Medical Instrument Co., Ltd.) will then be connected to enhance the acupuncture sensation based on the tolerance of the participant. Direct needling is the routine method for the PC6 and PC4 acupoints. Oblique needling is only used in cases requiring the penetrating needling technique. Therefore, this study will use the routine direct insertion method. Previous studies have demonstrated that continuous wave EA at a frequency of 20 Hz effectively increased blood flow in the ischemic area, reduced the infarct area, relaxed the muscles, relieved pain, decreased mortality, suppressed arrhythmias, and protected the myocardial tissue (40–43). Therefore, in this study, continuous wave EA stimulation at 20 Hz will be maintained throughout the PCI procedure and the current intensity will be adjusted based on the patient tolerance levels. Furthermore, experts will supervise and guide the operators throughout the experiment and promptly address any issues that may arise to ensure smooth progression of the surgeries. These measures will prevent any interference with the PCI procedure.

**Figure 2 F2:**
[figure not shown]
Location of acupoints.

### Outcome measurement

2.9

#### Primary outcome

2.9.1

The primary outcome is the incidence of SF-NR and will be calculated as follows: Incidence of SF-NR = (number of cases with no-reflow + number of cases with slow flow)/total number of cases × 100%. SF-NR will be determined based on the CTFC and TIMI flow grade criteria. Two experienced cardiologists will independently assess slow flow (TIMI grade 2 or CTFC > 27 frames) and no-reflow (TIMI grade 0–1 or CTFC > 40 frames) immediately after PCI stent implantation for patients without dissection, thrombus, or spasm (44). The recordings will be conducted at a rate of 30 frames per second, and the CTFC of the left anterior descending artery will be calculated by dividing the number of frames by 1.7 (45). In the case of disagreements, data will be reassessed jointly to reach a consensus.

#### Secondary outcomes

2.9.2

(1)*Cardiac biomarkers*: Assessments of serum high-sensitive cardiac troponin I (cTnI), myoglobin (Myo), creatine kinase-MB (CK-MB), and N-terminal pro-brain natriuretic peptide (NT-proBNP).(2)*Inflammatory biomarkers*: Assessments of leukocytes, neutrophils, lymphocytes, and high-sensitivity C-reactive protein (Hs-CRP).(3)*Chest pain score*: Chest pain severity will be assessed using the Numeric Rating Scale (NRS) with the participants rating pain on a 10-point scale, where 0 represents no pain, 1–3 indicates mild pain, 4–6 moderate pain, and 7–10 indicates severe pain.(4)*Anxiety score*: This will be evaluated using the Visual Analogue Scale for Anxiety (VAS-A) with 10-point scoring system where 0 indicates no anxiety, 1–3 indicates mild anxiety, 4–6 indicates moderate anxiety, and 7–10 indicates severe anxiety.(5)*Electrocardiogram examination*: Assessment of cardiac activity using the electrocardiograms.(6)*TCM symptom score*: Symptom severity grading will be based on the 2002 Guidance principle of clinical research on new drugs of Traditional Chinese Medicine (46). The severity grading categories are none, mild, moderate, and severe. Major symptoms will be scored as 0, 3, 6, or 9 points. The secondary symptoms will be scored as 0, 1, 2, or 3 points. The specific scores are shown in the Supplementary Material. TCM symptom score = major symptoms score + secondary symptoms score. The efficacy index will be calculated using the following formula: [(Score at initial admission - Score at 24 h after PCI)/Score at initial admission] × 100%. The efficacy index is classified into the following three grades: ineffective (0%–30%), effective (30%–70%), and significant (70%–100%). Total effective rate = significant effective rate + effective rate.(7)*MACCE*: The incidences of major adverse cardiovascular and cerebrovascular events (MACCE) include hemorrhage, recurrent myocardial infarction, revascularization, readmission, and cardiogenic death during the follow up within one month after PCI.

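### The TCM symptom score is a numeric sum, but the only efficacy results defined for it are three percent-change grades and a yes/no rate; testing either would lose a substantial share of its information

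*Protocol article*

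**What the plan says.** Section 2.9.2(6) of the protocol article scores major symptoms 0, 3, 6 or 9 and secondary symptoms 0, 1, 2 or 3, and adds them: "TCM symptom score = major symptoms score + secondary symptoms score". The score is therefore a numeric quantity with many possible values.

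The section then defines an efficacy index as a percentage fall from admission, "Score at initial admission - Score at 24 h after PCI)/Score at initial admission] × 100" per cent, and grades it: "The efficacy index is classified into the following three grades: ineffective (0%–30%), effective (30%–70%), and significant (70%–100" per cent). The top two grades are merged: "Total effective rate = significant effective rate + effective rate". No other efficacy result is defined for this outcome.

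Section 2.15 gives tests by type of data and does not name this outcome:
- Normally distributed data: "independent sample t-tests and paired t-tests will be used within-group comparisons", the independent test being for between-group comparison. Non-parametric tests apply otherwise.
- Ordinal data: "Ridit analysis or rank sum tests will be used to assess the ordinal data".
- Counts: "Count data will be expressed as frequency (percentage) and analyzed using the chi-square test".

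Table 1 schedules the score preoperatively and at 72 h. It has no 24 h column.

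**The concern.** Cutting a numeric measure at 30% treats improvements of 31% and 95% as the same result, and improvements of 29% and 31% as opposite results. Sections 2.9.2(3) and (4) also give severity bands, for pain and anxiety, but define no response rate from them. Only the TCM score is carried through to a yes/no efficacy figure, so a reader would take that figure, or the grades, as the intended result.

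Two stated purposes are affected. The Discussion says the score will be used to judge therapeutic effect, and Section 2.12 says the pilot is to supply effect sizes for later trials. A response rate is a weak basis for both. If most patients in both arms improve by more than 30% after PCI, the rate would sit near its ceiling and could hardly separate the arms.

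**Working it through.** **Inputs from the article.** Cuts at 30% and 70% (Section 2.9.2(6)). There are 25 evaluable patients per arm, raised for 20% dropout as 25 × 1.20 = 30 per arm, or 60 in total (Section 2.12). On significance, P "< 0.05 will be considered as a statistically significant difference between groups" (Section 2.15). The article gives no power, SD, responder rate or effect size for this outcome, so there is no figure of its own to reproduce.

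**Assumptions.** Normal index with equal SDs; standardised difference d of 0.5 or 0.8; control total effective rate 50-80%; two-sided 5% level (the article does not state sidedness).

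**1. Information kept by the yes/no rate.** Relative to the uncut normal index this is φ(c)² / [p(1−p)], where p is the responder rate, c the normal quantile of p and φ the normal density.

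| p | kept | lost |
|---|---|---|
| 50% | 0.637 | 36% |
| 70% | 0.576 | 42% |
| 80% | 0.490 | 51% |
| 90% | 0.342 | 66% |

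Example at 50%: 0.3989² / 0.25 = 0.637. The value reaches one half at p = 0.79 and, by symmetry, 0.21.

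**2. Information kept by three grades under a rank or Ridit test.** With optimal scores this is the sum over grades of (difference in φ at the grade's two limits)² / (grade proportion). Rank scores give nearly the same values. For proportions ineffective/effective/significant:
- 27/46/27: 2 × 0.331² / 0.27 = 0.81
- one third each: 0.79
- 50/40/10: 0.74
- 10/80/10: 0.62
- 70/25/5: 0.61

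The loss is about 19% to 39%.

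**3. Power, 25 per arm.**
- Uncut index: Φ(d√(n/2) − 1.96). For d = 0.8 this is Φ(0.8 × 3.536 − 1.96) = Φ(0.868) = 80.7%.
- Rate: the EA rate is p₂ = Φ(c + d), and power is Φ{[|p₂ − p₁| − 1.96√(2p̄(1−p̄)/n)] / √([p₁(1−p₁) + p₂(1−p₂)]/n)}. For d = 0.8 and p₁ = 50%, p₂ = 79% and power is 57.0%.

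| Control rate | EA rate (d = 0.8) | Power of rate, d = 0.8 | Power of rate, d = 0.5 | n per arm for 80% power, d = 0.8 |
|---|---|---|---|---|
| 50% | 79% | 57.0% | 27.7% | 43 |
| 60% | 85% | 52.3% | 26.1% | 48 |
| 70% | 91% | 45.3% | 23.3% | 57 |
| 80% | 95% | 35.6% | 19.4% | 76 |
| Uncut index | – | 80.7% | 42.4% | 25 |

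With 30 per arm and d = 0.8, the uncut index has 87.3% power, against 65.1% for the rate at a control rate of 50% and 41.5% at 80%.

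**4. Simulation check** (4,000 trials per setting, index capped at 100%, cuts at 30% and 70%, d = 0.8, 25 per arm). The t-test had 78-80% power and the three-grade rank test 65-70%. Chi-square on the rate had 62%, 53%, 41% and 7% at control rates of 50%, 65%, 79% and 93%.

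**5. Edges of the grades.** Scores are whole numbers, so exact hits can occur. A fall from 10 to 7 is 30% and a fall from 10 to 3 is 70%, and each lies in two grades. The grades start at 0%, so a patient who worsens has no grade. An admission score of 0 gives no index.

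**The case against.** The strongest reply is that the numeric score has not been displaced. The listed outcome is the TCM symptom score itself, and the generic rules in Section 2.15 for numeric data can be applied to it. This stands. A reader might infer that the plan rules out a numeric comparison, or that no mean difference or SD will be available for planning. The article does not say so: if the score is summarised as mean ± SEM, the SD is SEM × √n.

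Second, the three grades are ordinal, so the rank or Ridit rule fits them better than chi-square. This also stands, and it is why the grades and the rate are sized separately above.

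Third, a reader might infer that the cut throws away most of the information, or that it does so because the sample is small. Neither is supported. The grades kept about 61-81% in every split tried. The rate keeps less than half only above about 79% or below about 21% responders, and the article gives no expected rate. The proportion lost does not depend on sample size; a small sample only makes the loss harder to afford.

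Fourth, the choice of test may belong in an unseen SAP, and the 2002 guidance and the supplement are not at hand. This does not remove the point. The article itself fixes the index, the cuts and the rate, and says nothing of a numeric efficacy result beside them. Division by the patient's own baseline is common to all percent-change measures and is not counted here as an error.

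**Conclusion.** The point holds as a conditional one. The article defines efficacy on this score only through grades and a rate, and leaves open what is tested. If the rate is tested, about 36-42% of the information is lost at responder rates of 50-70%; if the grades are tested, about 19-39%. At d = 0.8 and 25 per arm, the formulas put the rate about 24 to 45 power points below the uncut index (80.7 − 57.0 and 80.7 − 35.6). The simulated three-grade rank test falls roughly 10 to 15 points short.

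These figures rest on an assumed normal index and on assumed effects and responder rates. They compare the uncut index with its cut versions; any further gain from baseline adjustment was not computed, because the article gives no correlation between admission and later scores. The overlapping endpoints, the missing grade for worsening and the 24 h/72 h mismatch need no assumption.

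Priority is minor to moderate: this is one of seven secondary outcomes in a pilot with no formal power calculation.

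**What to change.** In Sections 2.9.2(6) and 2.15:
- Make the main analysis of this outcome the between-arm difference in the numeric post-PCI TCM symptom score, from a linear model with the admission score as covariate. Use a rank-based version if residuals are badly skewed. Report the difference with its 95% CI, and the SD.
- Report the three grades and the total effective rate as descriptive percentages without their own test. Make the grade limits mutually exclusive and say where a worsened patient is counted.
- Reconcile the assessment time between the index formula (24 h after PCI) and Table 1 (72 h), and name that time in the analysis.

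The analysis change is wording only and needs no extra patients. Reconciling the time needs no new visit if the score is already being taken at the time finally named. The small downside is that the customary total effective rate is no longer the tested result, though it remains reported for comparison with other TCM studies.
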